## Abstract

**Background:**

More than 2 billion peripheral vascular cannulas are introduced globally each year. It is the most frequently performed invasive procedure in medicine worldwide. There is a group of patients with difficult intravenous access (DIVA). In experts’ hands, ultrasound-guided vascular access appears to be a significantly better method. Investigators hypothesize that UGVA is superior also in short-term patency of cannula and even for blood draw through cannula. Repeated cannula pricks in the operating room setting not only puts a lot of stress on the patient and medical staff, but they also waste OR time.

**Methods:**

This investigator-initiated prospective randomized monocentric controlled trial is designed to randomly allocate 200 patients undergoing elective primary total joint arthroplasty of hip or knee to one of two groups as follows: Group C (control group) – peripheral venous cannula insertion by palpation or Group USG (intervention) – cannula insertion by ultrasound-guided vascular access. Our primary endpoint is to compare the number of attempts for ultrasound-guided insertion of the peripheral venous cannula with common palpation insertion of the peripheral venous cannula in overweight/obese patients (BMI ≥ 25). The secondary endpoint is a failure rate of the peripheral venous cannula to administer intravenous therapy up to 5 days postoperatively. Tertiary endpoints include a portion of long PVCs that are able to ensure blood draw up to 5 days postoperatively, time needed to insert PVC in each group, number of needle tip redirections in both groups, and reinsertion of PVC needed in both groups for any reason.

**Discussion:**

This study is pragmatic and is looking for clinically relevant data. After completion, it will answer the question of whether it is clinically relevant to use ultrasound-guided vascular access in the context of not only short-term benefit of insertion, but also up to 5 days after insertion. Also, if this method can ensure blood draw through a peripheral vein cannula, it can save resources in the perioperative period — valuable especially considering the ongoing shortage of medical staff worldwide. If this hypothesis is confirmed, this finding could contribute to more widespread implementation of ultrasound-guided peripheral vascular access in the perioperative period.

**Trial registration:**

ClinicalTrials.gov NCT05156008. Registered on 13.12.2021.

## Administrative information

Note: the numbers in curly brackets in this protocol refer to SPIRIT checklist item numbers. The order of the items has been modified to group similar items (see http://www.equator-network.org/reporting-guidelines/spirit-2013-statement-defining-standard-protocol-items-for-clinical-trials/).

## Introduction

### Background and rationale {6a}

There is a group of patients with difficult intravenous access (DIVA). In experts’ hands, ultrasound-guided vascular access appears to be a significantly better method. Investigators hypothesize that UGVA is superior also in short-term patency of cannula for up to 5 days and even for blood draw through cannula. In overweight/obese orthopedic patients the DIVA subpopulation can reach up to 50% [1, 2]. Ultrasound seems to facilitate vascular access in patients with higher BMI [3]. The classic landmark technique becomes very difficult in the higher BMI ranges, whereas ultrasound is mostly unaffected by BMI [4]. In our hospital, we perform over 1.000 joint arthroplasties annually. In a small internal hospital audit (*n* = 34) we found out that 60% of inserted cannulas that adhered to strict insertion protocol (Fig. 1) under ultrasound, ensured blood draw on POD (post operative day) 1 and 2. If we can insert a low-cost long PVC that can last up to 5 days and allows for blood drawing, it will ease the perioperative period for DIVA patients and medical staff as well. To the best of our knowledge, no randomized controlled trials have yet been performed to study the effect of ultrasound-guided vascular access of long PVCs in orthopedic overweight patients with focus on i.v. access patency up to 5 days and the ability to draw blood through PVC. Ultrasound can reduce the number of attempts and complications as well, but only in the experienced hands of a fully trained UGVA specialist. Repeated cannula insertions not only put a lot of stress on patients and medical staff. They also waste OR (operating room) time and use up the veins of the patient, which may never heal [5] and this makes vein punctures even more difficult in the future.

**Fig. 1 Fig1:**
[figure not shown]
Insertion manual

### Objectives {7}

The primary objective of this investigator-initiated prospective randomized controlled trial is to compare the number of attempts for ultrasound-guided insertion of PVC with common palpation insertion of PVC in overweight/obese patients. The secondary objective is the comparison of long PVCs and “regular” short PVCs in terms of their ability to administer intravenous therapy through the cannula up to 5 days postoperatively. Tertiary objectives are a portion of long PVCs that are able to ensure blood draw up to 5 days postoperatively, time needed to insert PVC in each group, number of needle tip redirections in both groups, and reinsertion of PVC needed in both groups for any reason.

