## Statistical methods

### Statistical methods for primary and secondary outcomes {20a}

The primary and secondary outcomes will be evaluated using the *χ*^2^ test in terms of the difference in approaches of cannula insertion between groups in the number of punctures and the failure rate of the cannulas (failure rate is defined as the proportion of cannulas requiring reinsertion within 5 days after insertion). RR and 95% confidence interval of successful venous cannulation will be also calculated. The primary endpoint is the number of attempts to successful cannulation determined by the number of skin punctures. More attempts are associated with complications. As a secondary endpoint, the failure rate is calculated from the ratio of cannulas that did not fail to cannulas that failed for any reason in each group, up to the first 5 days postoperatively. This data is obtained from the patient protocol (Fig. 2). Primary and secondary outcomes will be reported as frequencies and percentages. For our tertiary outcome, to compare differences between the intervention groups (time required for cannula insertion, number of cannulas used, A-DIVA scoring system, etc.), *t*-test for independent groups or Mann–Whitney U test will be used, if data are not normally distributed. The effect of the intervention on outcome variables will be determined by using paired *t*-test or Wilcoxon signed-rank test for data obtained at baseline and for 5 days of the study. Other endpoints include portion of long PVCs that are able to ensure blood draw up to 5 days postoperatively, time needed to insert PVC in each group, reinsertion of PVC needed in both groups for any reason. All this data is recorded in the study protocol.

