### Limitations

In order to obtain relevant data, it is necessary to ensure vascular access in both groups by experienced and professionally trained staff. Otherwise, there might be misleading data through the whole study.

DIVA is a widespread problem in many patient groups. We chose orthopedic patients scheduled for total hip- or knee- arthroplasty due to a relatively similar patient population, high patient turnover, higher rates of obesity (which is an inclusion criterion), and most importantly, the electivity of the procedure.

The difference between the types of needle/cannula used in the classic method and the USG method reflects both the different nature of the veins being cannulated (superficial vs. deep), as well as the clinical practice in our institution.

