### Strenghts

“Classical” Vasofix needles used in the control group are widely and routinely used by our staff when cannulating veins preoperatively. Deep Introcan needles are in turn used in sonography due to the longer length of the needle required to reach the deeper veins in the forearm and upper arm. Thus, we are comparing the gold standard of the classic method with the gold standard of the USG method. If we would use the same needle in both groups, one group would necessarily receive inferior care – biasing our results and potentially damaging our patients. Study is also focused on not just vascular access obtaining but also on vascular access durability in relation to UGVA. UGVA allows to choose better place to site peripheral vein cannula in comparison with palpation technique which might translate in to lower complication rates [11]. All of these measurements have a great impact on how long this low-cost cannula lasts in DIVA patients [12].

The choice of our outcomes is a comprehensive list of all the potential benefits of USG cannulation: reducing the number of patient pricks for needle insertions and blood draws — increasing satisfaction and reducing complications; reducing time spent in the OR to facilitate increased patient turnover; using less material and saving manpower — making it an economical procedure. 

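### Superiority of ultrasound access for blood draw is hypothesised, but the blood-draw endpoint covers only long cannulas, which only the ultrasound arm receives, so the hypothesis cannot be tested

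*Protocol article*

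**What the plan says.** **Hypothesis.** Background and rationale {6a} states: "Investigators hypothesize that UGVA is superior also in short-term patency of cannula for up to 5 days and even for blood draw through cannula". The Background paragraph of the Abstract makes the same claim without the 5-day horizon.

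**Blood-draw endpoint.** It is worded for long cannulas in three places:
- Objectives {7}: "Tertiary objectives are a portion of long PVCs that are able to ensure blood draw up to 5 days postoperatively"
- Abstract, Methods: "Tertiary endpoints include a portion of long PVCs that are able to ensure blood draw up to 5 days postoperatively"
- Statistical methods {20a}: "Other endpoints include portion of long PVCs that are able to ensure blood draw up to 5 days postoperatively"

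In the Abstract and Objectives sentences, insertion time, needle redirections and reinsertions are each specified for the two groups. Blood draw is not.

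**Devices.** The Strengths section says "Vasofix needles used in the control group are widely and routinely used by our staff" and assigns the longer Deep Introcan to sonography. The Limitations section acknowledges "The difference between the types of needle/cannula used in the classic method and the USG method" and gives reasons for it.

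**Patency.** Objectives {7} words the secondary objective as a "comparison of long PVCs and “regular” short PVCs in terms of their ability to administer intravenous therapy". Statistical methods {20a} compares it between the groups with a chi-square test, where "failure rate is defined as the proportion of cannulas requiring reinsertion within 5 days after insertion".

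**The concern.** Superiority is a statement about two groups. An endpoint restricted to a device used in only one of them cannot support or refute it, however large the trial. The randomisation contributes nothing to that endpoint.

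At stake is one of the trial's stated reasons for existing. The Abstract's Discussion links blood draw through the cannula to saving resources in the perioperative period, and then to wider uptake of the method if the hypothesis is confirmed. If blood draw is never assessed in controls, the missing comparison cannot be recovered once the patients have gone home. A high proportion in the ultrasound arm could then be read as an advantage that nobody measured.

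The patency wording raises a lesser problem of labelling. One section credits ultrasound and another credits cannula length, while the arms differ in both.

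**Working it through.** **1. Who is in the blood-draw denominator?**
- Endpoint population: long cannulas (Abstract Methods; Objectives; Statistical methods).
- Long cannula: the Deep Introcan, used with sonography (Strengths).
- Control device: Vasofix (Strengths). The secondary objective confirms the pairing by setting long against regular short cannulas.
- Control patients in the denominator as written: none.

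**2. Does the plan have its own figure for this endpoint?** There is no planned effect and no control rate. The only figure is the internal audit in Background and rationale {6a}: 60% of ultrasound-inserted cannulas allowed a draw on postoperative days 1 and 2, n = 34. If all 34 form the denominator, that is about 20/34, with a Wilson 95% interval of 42% to 74%. The audit is also single-arm. The sample size {14} rests on first-insertion failure (20% against 5%), so it does not address blood draw.

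**3. What would the trial deliver as written?** Assume equal allocation of 200 patients, so n = 100 in the ultrasound arm, and take p = 0.60 from the audit for illustration. Wilson interval with z = 1.96, z² = 3.8416:
- centre = (p + z²/2n) / (1 + z²/n) = (0.60 + 0.0192) / 1.0384 = 0.596
- half-width = z √[p(1−p)/n + z²/4n²] / (1 + z²/n) = 1.96 × √(0.0024 + 0.000096) / 1.0384 = 0.094
- interval = 50.2% to 69.1%

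This describes one arm. No difference, ratio or test follows from it.

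**4. What would recording controls add?** Take 100 per arm, 60% in the ultrasound arm, two-sided 5%, and

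power = Φ{[d√n − 1.96 √(2p̄(1−p̄))] / √[p₁(1−p₁) + p₂(1−p₂)]},

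where d is the difference and p̄ the mean of the two rates. For an assumed control rate of 40%: (0.20 × 10 − 1.96 × 0.7071) / 0.6928 = 0.886, so power is 81%. Because the documents give no control rate, a range is needed:

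| Assumed control rate | Power |
|---|---|
| 35% | 95% |
| 40% | 81% |
| 45% | 57% |
| 50% | 29% |

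The planned size would detect a large difference in blood draw, but not a modest one.

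**5. Patency, side by side.**
- Background and rationale: ultrasound access is superior for patency.
- Objectives: long against short cannulas.
- Statistical methods: failure within 5 days, compared between the groups.
- Limitations and Strengths: each method is paired with its usual device, and target veins are superficial in one arm and deep in the other. Section {17a} adds that fixation differs.

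The test compares randomised groups and is valid for the whole package. It cannot separate guidance from cannula length, so neither single-factor wording fits it.

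**The case against.** **Feasibility reading.** The Abstract's Discussion asks only whether the method can make blood draw possible, and the rationale speaks in the same conditional way. A proportion among long cannulas answers that question. This stands as a defence of a descriptive endpoint. It does not rescue the hypothesis, which claims superiority in both the Abstract and the rationale.

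**Condensed article.** The data form (Fig. 2) is not shown and may record blood draw in controls. The exact denominator may also be set in a fuller document. Both are fair, and the missing denominator detail is not held against the plan. But the endpoint is stated in three places and each time leaves controls out. If control data are being collected, the text still needs correcting.

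**Patency.** A reader might infer that no patency conclusion is possible because the cannulas differ. The documents do not support that. Five-day failure is compared between randomised groups, and Limitations and Strengths openly present each method with its customary device and explain why one needle was not used throughout. Wanting guidance isolated from device would be asking for a different trial.

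**Two further overreadings.** The Abstract does not announce superiority as a conclusion: it states a hypothesis and conditional implications. Nor can the audit's 60% be scaled down to a day-5 figure, because it refers to inserted cannulas on days 1 and 2 and the documents give no 5-day failure rate for the ultrasound arm.

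**Conclusion.** The point holds for blood draw. The superiority hypothesis has no control-arm endpoint and cannot be tested as written. The yield is a single-arm proportion, for example 60/100 with a 95% interval of about 50% to 69%. This rests on reading the long PVC as the device reserved for ultrasound insertion, which the Strengths section supports. The interval also assumes 100 patients per arm and borrows the audit rate.

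For patency only the wording is at fault. A randomised conclusion about ultrasound guidance with a long cannula against palpation with a short one is available. A conclusion about guidance alone or length alone is not.

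The matter affects a tertiary endpoint and leaves the primary analysis untouched. It merits correction before recruitment because control data not recorded prospectively are lost.

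**What to change.** **Preferred.** Define blood-draw success in both randomised groups, record it at the same daily checks and compare the arms.
- Denominator: all randomised patients.
- A failed cannula counts as not able to draw.
- A cannula still working at discharge or elective removal does not count as a failure. This matters because section {18b} ends follow-up at discharge when that comes before day 5. Scoring every removed cannula as unable to draw would turn early discharge into failure.
- Since the trial is not sized for this outcome, report the between-arm difference with its confidence interval.

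**If controls will not be assessed.** Delete the superiority wording for blood draw from the Abstract and the rationale, and report a single-arm proportion with its interval.

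**Accompanying wording change.** State the patency hypothesis and the secondary objective in the same terms: ultrasound guidance with a long PVC versus palpation with a short PVC.

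**Cost.** The second option and the patency change are text only. The first adds one item per check in control patients. How much work that is cannot be judged without the data form. In every case the claim becomes narrower, or better supported.

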### Trial design {8}

This investigator-initiated prospective randomized parallel groups monocentric controlled trial is designed to enroll 200 patients. There is no blinding because cannulas are easy to distinguish.

## Methods: participants, interventions, and outcomes

### Study setting {9}

This study is conducted in a single center, in the clinical settings of the Orthopaedic Department of F. D. Roosevelt University Hospital and Operating Rooms by medical staff of the Anesthesia and Intensive Care Department of F. D. Roosevelt University Hospital.

### Eligibility criteria {10}

Inclusion criteria are (1) age group of 18–75 years, (2) body mass index > 25, and (3) primary hip or knee arthroplasty. Exclusion criteria are as follows: (1) reoperation of arthroplasty, (2) mental disorder, (3) sepsis, (4) protocol non-compliance, (5) pregnancy, and (6) patient refusal or no informed consent or both. Interventions are performed by anesthetists trained in UGVA.

### Who will take informed consent? {26a}

Patients scheduled for elective primary total joint arthroplasty of hip or knee surgery in F. D. Roosevelt University Hospital in Banska Bystrica, Slovakia will be asked for written informed consent by a member of the Anesthesiology or Orthopedics Department during preoperative assessment.

### Additional consent provisions for collection and use of participant data and biological specimens {26b}

Not applicable, we do not want to use data in another study. No specimens are collected.

## Interventions

### Explanation for the choice of comparators {6b}

Classic palpation approach for vascular access is challenging in DIVA patients. Up to 50% of orthopedic patients are DIVA [1, 2] and orthopedic surgeries are on the rise in developed countries. Medical staff can site venous cannula only to veins they can see. Therefore, the cannula is often in a suboptimal place of flexion of the arm in the wrist or elbow which are associated with complications [6, 7] and higher failure rates up to 63% [8].

Ultrasound enables us to place the cannula in an ideal place, in terms of the complications mentioned above. In addition, we can measure the diameter of the vein and use cannula width that will obscure only one third of the internal lumen. This should allow for blood draw because of undisturbed bloodstream in the vein.

We chose the UGVA approach in comparison to the classic palpation approach in standard clinical settings. This design of study allows to compare the standard of care (insertion of cannula by palpation) to the modern (ultrasound-guided insertion of cannula), technically more challenging but also a more rewarding option.

### Intervention description {11a}

All patients in the ultrasound group will receive a prick by an UGVA experienced physician in the block room, preoperatively. The time measurement starts with prescan of the forearm and then, if no suitable vein is found, the anesthetist will prescan the upper arm. Under strict antiseptic precautions, after preparation of the skin with 2% Chlorhexidine (Chlorhexidine, BBraun, Germany) and sterile cover of probe Dermafoil (Dermafoil, Batist, Czech Republic), the introduction of the cannula is carried out by anesthetist. The entire procedure follows our study protocol, using out of plane technique with constant clear visualization of the needle tip, which is slowly advanced all the way into the vein. The procedure may be performed with or without a tourniquet following the insertion manual (Fig. 1). Another researcher makes notes into the study protocol (Fig. 2).

**Fig. 2 Fig2:**
[figure not shown]
Protocol

### Criteria for discontinuing or modifying allocated interventions {11b}

The procedure may be performed with or without a tourniquet following the insertion manual (Fig. 1). The method should be discontinued after two unsuccessful attempts and another experienced practitioner should be sought. If such a practitioner is not available it has to be marked in the protocol as “failure” with a note “no experienced practitioner available.” Another researcher makes notes into the study protocol (Fig. 2).

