### Sample size {14}

The estimate for the final sample size was based on the expected drop-out rate and the objective and design of the study. This trial assumes a comparison of the effect on outcome variables in peripheral vein insertion in the USG group and palpation-inserted peripheral venous cannula as the control group. In overall, we hypothesize that it will take fewer attempts to insert the cannula into a vein with the USG technique (USG: 1 vs. C: 1–3), corresponding to a reduction in time of ≥ 3 min (clinically relevant indicator) for successful cannulation in the USG group. When calculating the sample size, based on our experience and literature data, we assumed a 20% risk of complications inserting the cannula into a vein in the standard way, 5% as a probability of a Type I error (α < 0.05), and the power of the test 90% (β = 0.10). Theoretically, we also accepted a 5% risk failure of a first insertion of a cannula into a vein in the USG group. The sample size calculation was based on the result of the risk ratio (RR) between groups as % of complications (unsuccessful prick) with cannula insertion into the peripheral veins [9]. The adequate sample size of 162 patients was calculated as described previously [10], increased by 20% for the case unforeseeable circumstances (technical error, data loss, poor patient cooperation, etc.) and rounded ≅ 200.

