## Discussion

Ultrasound-guided vascular access is an essential skill in modern anesthesia practice. It is recognized also by medical faculties; therefore, in some countries, they include this skill into student’s curriculum. In the beginning of training, it is time-consuming although as the operator gets enough practice whole insertion process takes only seconds. This is the biggest challenge. To ensure that there is always a physician/nurse that is proficient in UGVA.

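### After two failed attempts, the only stated trigger for recording failure is that no second practitioner is free, so the RR of successful cannulation mixes staffing and rescue with technique

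*Protocol article*

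**What the plan says.** **Protocol article, {11b} (discontinuing or modifying interventions).** "The method should be discontinued after two unsuccessful attempts and another experienced practitioner should be sought". Then: "If such a practitioner is not available it has to be marked in the protocol as" a failure, with a note giving the missing practitioner as the reason. The section does not say how to record a patient in whom the second practitioner succeeds, also fails, or uses the other technique.

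**{20a} (statistical methods).** "The primary endpoint is the number of attempts to successful cannulation determined by the number of skin punctures". In addition, "RR and 95% confidence interval of successful venous cannulation will be also calculated". Success is not tied to the allocated method or to the first operator. The secondary outcome uses a different failure: "failure rate is defined as the proportion of cannulas requiring reinsertion within 5 days after insertion".

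**{14} (sample size).** One attempt is expected with ultrasound and one to three in control. For control, "we assumed a 20% risk of complications inserting the cannula into a vein in the standard way"; for the ultrasound (USG) group the article accepts a 5% failure of the first insertion.

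**Discussion and Limitations.** The Discussion names one main difficulty with ultrasound-guided vascular access (UGVA): "To ensure that there is always a physician/nurse that is proficient in UGVA". The Limitations say that "it is necessary to ensure vascular access in both groups by experienced and professionally trained staff".

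**The concern.** The recording rule in {11b} makes an outcome label depend on something other than the outcome. Take two patients in the same arm, each with two failed attempts by the allocated method. If a colleague is free, the patient goes on to a further puncture and may end up as a successful cannulation. If nobody is free, the patient is a failure. The technique performed identically in both.

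The rescue step adds a second problem. {11b} does not restrict the technique of the second practitioner, and {10} has interventions done by anesthetists trained in UGVA. A palpation patient could be rescued with ultrasound and still be counted as a success in the palpation arm.

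The planned RR would then describe technique, rescue and rota together. The trial is unblinded ({17a}), which is a further reason not to let a label turn on circumstance. The two statements about attempts also need reconciling: if the method stops at two, a third control attempt falls after that stop, and the article does not say whose attempt it is.

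**Working it through.** **Inputs from the article.** First-attempt failure 20% (control) and 5% (USG), from {14}. For control the article calls this the risk of complications, meaning an unsuccessful prick; I read it as first-attempt failure.

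**The plan's own figure.** These two rates underlie the stated 162. With 1:1 allocation, 5% alpha, 90% power and the pooled formula, one-sided:

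n per arm = [1.645·√(2·0.125·0.875) + 1.282·√(0.20·0.80 + 0.05·0.95)]² / 0.15² = 81.4, so 82 per arm, 164 in total.

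The unpooled one-sided version gives 158; the two-sided pooled version gives 202. The stated 162 lies near the one-sided results, so the two rates are the right ones to use here. The present point does not change the sample size.

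**Assumptions (the article gives none of these).** q = chance that the second attempt also fails; u = chance that no second practitioner is available; rescue always succeeds.

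**Formulas.** Two failed attempts: F = first-attempt failure × q. Recorded failure under {11b}: F × u. RR of success = (1 − F_USG·u_USG) / (1 − F_C·u_C). Coding on the allocated method is the case u = 1 in both arms.

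**Share of patients affected.**
- Independent attempts: 0.20² = 4% in control, 0.05² = 0.25% in USG.
- q = 50% in both arms: 10% and 2.5%.
- q = 100% (upper bound): 20% and 5%.

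**RR of success, USG over control.**

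| Second attempt | Coded on method | u = 10% in both | u = 10% C, 50% USG | u = 0% C, 100% USG |
|---|---|---|---|---|
| Independent | 1.0391 | 1.0038 | 1.0028 | 0.9975 |
| q = 50% | 1.0833 | 1.0076 | 0.9975 | 0.9750 |
| q = 100% | 1.1875 | 1.0153 | 0.9949 | 0.9500 |

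**Worked row, q = 50%.** Coded on method: 97.5% / 90% = 1.083. With u = 10% and 50%, recorded failure is 0.10 × 0.10 = 1.0% in control and 0.025 × 0.50 = 1.25% in USG, so recorded success is 99.0% and 98.75%, and the RR is 0.9975.

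**RR of failure in the same row.** Coded on method: 2.5% / 10% = 0.25. With equal u it stays 0.25, because u cancels. With u = 10% and 50% it is 1.25% / 1.0% = 1.25.

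Equal availability therefore preserves the failure ratio. It draws the success ratio toward 1, because recorded failures become rare, but it cannot reverse the direction. Reversal needs unequal availability.

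**The case against.** **A reader might infer that the article says ultrasound operators are scarcer.** It does not. The Discussion speaks of keeping UGVA proficiency available and makes no comparison with palpation; the Limitations ask for experienced staff in both groups. Any difference in availability between arms is an assumption. This objection stands.

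**A reader might infer that the outcome measures staffing instead of technique.** That goes too far. Technique decides who reaches two failed attempts, and few patients do so on the article's rates. This also stands.

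**The main outcomes are largely untouched.** The primary endpoint counts skin punctures, so a rescued patient still shows the extra ones; what is open is whose punctures count. The 5-day failure rate has its own definition. This stands, and it confines the problem to the RR of success.

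**The RR may mean first-insertion success.** {14} reasons in terms of an unsuccessful prick and a failed first insertion. On that reading, nothing after the second attempt could change the RR. The reading is possible, but {20a} does not state it.

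**The information may be recoverable.** Three or more punctures, or the failure mark with its note, would identify most patients with two failed attempts. The recording form (Fig. 2) is not shown and may hold more. This stands in part: the technique of the rescuer may not be recoverable if it was not written down. The full protocol may also cover a second practitioner who fails, so *only trigger* means the only one stated in the article.

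**The rule may cover ultrasound only.** {11b} opens with a sentence that also appears in the ultrasound description in {11a}. If so, only one arm could receive the label, which makes the coding less even between arms.

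**Conclusion.** The point holds in a limited form. {11b} fixes a recording rule under which identical technical results can be coded differently by staffing, and {20a} plans an RR of success not tied to the allocated method. That RR mixes staffing and rescue with technique, and a difference in rescue or its availability between arms would bias it. The article does not state such a difference.

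The affected share is about 4% of control and 0.25% of USG patients with independent attempts, and at most 20% and 5%. In the q = 50% illustration the RR of success moves from 1.08 to about 1.00. Over all the scenarios tabulated it runs from 0.95 to 1.19.

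A reader might take the values below 1 as a forecast that the effect will reverse. They are not. A clear reversal, such as 0.95, comes from the corner where every control patient and no USG patient finds a second practitioner. All of these figures rest on assumed availability, second-attempt failure and perfect rescue.

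**What to change.** Leave the care pathway as it is and change only the coding:

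- Record *allocated method unsuccessful* for every patient in either arm with two unsuccessful attempts by the first operator, whether or not a second practitioner is found.
- Compute the RR of successful cannulation on that variable.
- Record rescue operator, rescue technique and later punctures in separate fields.
- Reconcile the stop after two attempts in {11b} with the one to three control attempts in {14}, stating whose attempts count toward the puncture endpoint.

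This should be in place before the first patient is randomized, because an unrecorded rescue technique may not be recoverable later. The cost is one sentence of outcome coding, a few form fields, and slightly lower stated success rates.
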